##### Process evaluation

For the exploration of implementation aspects of exergaming the Measurement Instrument for Determinants of Innovations (MIDI) [59, 60] will be applied. The MIDI is survey that measures 29 items, scored on a 5-point Likert scale, covering determinants of innovations that may affect its implementation, along four domains: the intervention itself, in this case the exergame (e.g., the exergame is perceived useful), the user, in this case the professional at the day-care centre that will apply the exergame (e.g., the professional feels sufficiently skilled to operate the exergame), the organization (e.g., there is enough time available to operate exergame), and the socio-political context (e.g., the patient is motivated to use the exergame). Several MIDI items will be adapted for this trial to fit the anticipated goals, benefits and downfalls, and stakeholders involved, based on short interviews with the participating organizations. Also, strategies applied to support the implementation (e.g., organize instruction meetings or develop instruction materials) are surveyed. Data will also be gathered on the characteristics of the respondent (age, gender, discipline), type of exergame applied in the study, and level of experience with use and implementation of exergames.

The MIDI will be administered among staff of the day-care centres in the experimental group. Based on the results, these organizations will receive recommendations on how to enhance implementation, which are tailored to their specific situation and circumstances. Towards the end of the trial, they will be asked to fill this survey out again.

Based on these results of both survey rounds, qualitative in depth interviews (maximum amount will be four) with day-care centres will be conducted. That is to say, with the centres that implemented the exergaming intervention most successfully (i.e., who scored the highest on implementation determinants over time and/or report the highest usage of the exergame) and those, who implemented exergaming least successfully (i.e., who scored the lowest on implementation determinants over time and/or report the highest usage of the exergame). During the interview we will discuss what the most influential determinants are for the implementation of the exergame and which strategies can be best applied to cope with ‘barriers’ and make use of ‘drivers’ (factors which enhance implementation). At the end of the trial, we will organise focus groups with the persons involved (participants with dementia, informal caregivers, staff of day-care centres and exergame providers) to measure the satisfaction with the physical activities offered in the day-care centres and to discuss future possibilities with regard to optimizing implementation.

### Procedure and ethics

The protocol, procedure and informed consent of this research study are approved by the Medical Ethics Committee (METc) of the Amsterdam University Medical Centers (UMC), location VU University medical center (VUmc) (file number NL58227.029.16). Any amendments to the protocol will also be submitted to the METc for approval, and sent to the NTR. Participation is voluntary for the day-care centres, participants with dementia and their informal caregivers, and they can stop participation at any time without having to explain their reasons. All participating day-care centres will sign a declaration of participation. All participants with dementia and their informal caregivers will sign an informed consent form. Additionally, the consent form for the participant with dementia also will be signed by the informal caregiver or legal representative.

After informed consent has been obtained, interviews and tests will be done involving the participants with dementia and their informal caregivers on three different occasions: at the start, after three and 6 months. To reduce any bias resulting from the sequence of the outcome measures, the order of the outcome measures used during the interviews will be partly randomized for each interview. Trained researchers will interview and test the participants with dementia in the day-care centres. Informal caregivers will be interviewed by telephone, unless an informal caregiver prefers to be interviewed in person. During these 6 months, the informal caregivers will keep two care diaries. In these, they will register their own use of health care facilities and medicines, as well as that of the participant with dementia.

### Blinding

Due to the design of the study and the nature of the intervention, blinding of staff of day-care centres, participants with dementia and informal caregivers is not possible. Because there are a few different questions in the outcomes measures for the control and experimental group (i.e. questions about the exergaming intervention) interviewers could also not be blinded.

### Data management

Data management will be conducted according to principles of International Conference on Harmonisation of technical requirements for registration of pharmaceuticals for human use/ Good Clinical Practice [61]. Data will be coded and entered into a Castor [62] database specifically built for this trial, and which is only accessible for the research team. Five percent of the data entry will be checked to see if the rate of errors is below the range of 3%. If not, all data will be double entered and checked. Range checks for data values will be done to account for unexpected or erroneous outliers. The identification codes of the research participants consist of a number for the day-care centre they are visiting and a number for the participant with dementia/informal caregiver. The list of codes with names of participants with dementia and informal caregivers is stored in a separate administrative Access database, which is only accessible for members of the research team. The (coded) digital research data are stored for at least 15 years. The paper data from the participants will be kept until 5 years after publication and then destroyed. Data monitoring will be arranged through the METc of the Amsterdam UMC, location VUmc, to whom the research team will provide an annual report of the study.

### Project group and advisory committee

The project group has 12 members from different organizations and areas of expertise (eg, academic researchers from Amsterdam UMC and Vrije Universiteit Amsterdam, a physiotherapist from HilverZorg, a large care organization). This group meets every 3 months. The project also has an Advisory Committee, consisting of seven members, who meet every 6 months. Both groups discuss the ongoing research project, including any issues that may arise and solutions to contribute to promote continuation of the trial and dissemination strategies. Whereas members of the project group execute the research project, the Advisory Committee has an advising role.

### Analysis of the data

#### Effect evaluation

Descriptive statistics at baseline will be used to compare participants with dementia, informal caregivers and staff of day-care centres in the experimental group with the control group. This will provide information on the differences between the intervention and control group at the start of the study.

The baseline scores of the people, who drop out of the study will be compared to those, who remain in the study. This will provide information about selective drop-out. Participants, who drop out during the trial will be included in the main analysis by imputing their scores using multiple imputation.

The effectiveness of the intervention will first be examined by comparing percentages, or mean scores (Chi-Square test, Mann-Whitney U test and T-tests (*p* < 0.05). Second, we will use mixed model regression analysis which will take into account the effect of clustering on the level of the day-care canters, confounders and missing data. The regression analysis will be conducted in three steps. Firstly, an analysis will be carried out for the primary and secondary outcome measures. If any differences in variables related to the outcome measures between the experimental group and the control group are found at baseline, these are added as potential confounders to the model for each outcome measure to check whether the uncorrected Beta-coefficient (β) changes with more than 10%, which means that this variable will remain in the model as a confounder. Examples of potential confounders are type of exergaming equipment, amount of support from staff, severity of dementia etc. Finally, mixed model analysis will be conducted for each outcomes variable for both follow up measurements (three and 6 months) with the selected confounders included in the analysis.

The method of QUalitative INteraction Trees (QUINT) [63] will be used for subgroup analysis. This allows for the identification of subgroups for whom the effect of the intervention differs, for example differences related gender, age, ethnicity or severity of dementia. Cut-off values do not need to be defined beforehand. Based on the QUINT analysis, more specific advice can be formulated with regard to which type of participant or informal caregiver the intervention has a positive effect or not.

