**Methods:**

A cluster Randomized Controlled Trial (RCT), with economic and process evaluations alongside will be carried out. In the Netherlands, 24 day-care centres are randomized in the experimental or control group. The study group will consist of 224 dyads (community-dwelling participants with dementia and their informal caregivers), who are interviewed at baseline, and at 3 and 6 months of follow-up. The participant with dementia has to visit the day-care centre for at least two days per week, have a diagnosis of mild to moderate dementia and have an informal caregiver present, who is willing to participate. Societal cost data will be collected during interviews, using healthcare utilization diaries, and from day-care centres. The process evaluation will only involve the experimental group, and will include an online survey, qualitative interviews and focus groups.

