**Fig. 1 Fig1:**
[figure not shown]
Flow chart of the randomization of day-care centres

We will (if possible) arrange blocks of centres that are similar to one another (in terms of region and/or target group: i.e. severity of dementia, age of onset, ethnicity, group size in the day-care centre). This is to control for environmental factors that might possibly influence the outcomes. Within these blocks, day-care centres will be randomized by an independent researcher, using Random Allocation Software [48], to either the experimental (exergaming) group or control (regular activities) group (12 day-care centres per group). After randomization, the day-care centres will remain in the experimental or control group throughout the duration of the trial.

Day-care centres which already have the required exergaming equipment, will be paired up with a comparable day-care centre from the same or another care organization without the equipment. Then they will be randomized as a pair instead of as an individual day-care centre. If this pair is randomized in the experimental group, the day-care centre with the exergaming equipment will participate in the trial. Similarly, if this pair is randomized in the control group, the day-care centre without the equipment will participate in the trial. Day-care centres which do not have any exergaming equipment yet, can also be enrolled for randomization individually if they are willing and able to buy the exergaming equipment needed for the trial. This has to be confirmed, prior to randomization, and is intended to ensure they can still participate when they are randomized to the experimental group.

Day-care centres in both groups will each receive an allowance of at most € 1.125,-. When they recruit eight persons or more. They can decide themselves how they want to spend this, for example to pay their staff for the extra hours they have to put in to participate in the research project. Day-care centres in the experimental group may also put this amount towards the purchase of the exergaming equipment.

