### Sample size calculation

Since a high quality study evaluating the effect of a similar intervention on physical activity and mobility was not available when we were writing our protocol, we used previous results on exergaming regarding one of our secondary outcome measures (memory) for this power calculation [38]. We performed a power analysis based on a power of 80% and a difference of 2 (with a standard deviation of 4.6) between scores on the Mini-Mental State Examination (MMSE) [50]. We chose an Intracluster Correlation Coefficient (ICC) of 0.05. This resulted in a sample size of 166 participating dyads with an alpha of 0.05. When also taking into account the cluster effect of the day-care centres (7 dyads per cluster) and drop out (4%), the total sample size needed is 224 dyads.

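### The first-step tests of effectiveness ignore the randomised day-care centres, so their nominal 5% level is about 8.6% to 10.0% under the protocol's own ICC

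*Protocol article*

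**What the plan says.** The centre is the unit of randomisation. The abstract states that "In the Netherlands, 24 day-care centres are randomized in the experimental or control group", and the section on recruitment and randomisation of centres gives "12 day-care centres per group". The Sample size calculation section expects outcomes to be correlated within a centre ("We chose an Intracluster Correlation Coefficient (ICC) of 0.05") and enlarges the sample for that reason.

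The Effect evaluation section describes the analysis of effectiveness in two stages. The first is: "The effectiveness of the intervention will first be examined by comparing percentages, or mean scores (Chi-Square test, Mann-Whitney U test and T-tests", with a threshold of p < 0.05. The next sentence reads: "Second, we will use mixed model regression analysis which will take into account the effect of clustering on the level of the day-care canters", and adds confounders and missing data. The paragraph ends with a mixed model for each outcome at both follow-up times.

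The first stage is presented as an examination of effectiveness. It is not called descriptive, although the same section uses that term for the baseline comparison. No cluster adjustment is attached to it.

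**The concern.** The ordinary t-test, Mann-Whitney U test and chi-square test treat every dyad as an independent observation. When whole centres are allocated and dyads in a centre resemble each other, the difference between arms varies more from trial to trial than these tests assume. Their standard errors are then too small and their p-values too low.

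The protocol accepts this correlation when it sets the sample size and then drops it in the first test of effectiveness. As written, an outcome examined both ways receives two p-values under the same heading, and only the second respects the design. What is at stake is that a first-stage p below 0.05 is reported or read as evidence of effectiveness when its real false-positive rate is well above 5%.

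**Working it through.** **Inputs from the protocol article**
- 24 centres, 12 per arm (abstract; recruitment and randomisation of centres).
- Difference 2, SD 4.6 on the MMSE, power 80%, alpha 0.05, ICC 0.05, 7 dyads per cluster, 4% drop-out, 224 dyads in total (Sample size calculation).
- Sidedness is not stated. A two-sided test reproduces the protocol's figure; a one-sided test would give 132 dyads.

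**Reproducing the sample size**
- Unclustered total = 4 × (1.960 + 0.842)² × 4.6² / 2² = 166.1, against the stated 166. Rounding up within each arm gives 2 × 84 = 168.
- Design effect DE = 1 + (m − 1) × ICC = 1 + 6 × 0.05 = 1.30.
- 166 × 1.30 = 215.8, and 215.8 / 0.96 = 224.8, against the stated 224.

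The protocol's figure is reproduced, which confirms that it rests on a two-sided 5% test and a design effect of 1.30.

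**Cluster size**

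The text states 7 per cluster, but 224 dyads in 24 centres is 224/24 = 9.3 per centre. Both are carried forward.

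**True size of a nominal 5% test that ignores the centres**

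The naive standard error is too small by the factor √DE, so
- true size = 2 × [1 − Φ(1.96/√DE)]
- understatement of the standard error = 1 − 1/√DE

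| ICC | Dyads per centre | DE | True size |
|---|---|---|---|
| 0.05 (protocol) | 7 | 1.30 | 8.6% |
| 0.05 (protocol) | 9.3 | 1.417 | 10.0% |
| 0.01 (assumed) | 7 | 1.06 | 5.7% |
| 0.01 (assumed) | 9.3 | 1.083 | 6.0% |
| 0.10 (assumed) | 7 | 1.60 | 12.1% |
| 0.10 (assumed) | 9.3 | 1.833 | 14.8% |

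At ICC 0.05 the steps are:
- m = 7: √1.30 = 1.140; 1.96/1.140 = 1.719; size 8.6%; standard error too small by 1 − 1/1.140 = 12.3%.
- m = 9.3: √1.417 = 1.190; 1.96/1.190 = 1.647; size 10.0%; standard error too small by 1 − 1/1.190 = 16.0%.

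**Check by simulation**

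With 12 centres per arm, ICC 0.05, no true effect and normal outcomes, the t-test rejected in 8.6% of runs (7 per centre) and 10.0% (9 or 10 per centre) over 20,000 runs. The Mann-Whitney test rejected in 8.0% and 9.6% over 8,000 runs. The chi-square test was not simulated; the same approximation applies to a proportion with the same ICC. A t-test on the 24 centre means, with 9 dyads per centre, stayed between 4.7% and 5.3%.

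**The case against.** The strongest reply is that the next sentence of the protocol brings in a model that allows for clustering, and that the paragraph ends with that model for every outcome. The natural reading is a crude look followed by the principal analysis. Much of this stands. The second-stage p-values are not affected.

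A reader might infer from the first stage that the trial's false-positive rate is roughly doubled. The documents do not support that. It would follow only if the naive tests alone decided effectiveness, and no passage says so. A rule for which analysis prevails is also something an article commonly leaves to the statistical analysis plan, so its absence is not counted here. The objection is to a test that the article does state, with its purpose and its threshold.

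Three further points qualify the size:
- The ICC of 0.05 was chosen for a calculation based on the MMSE, and no ICC is given for physical activity or the SPPB. At 0.01 the inflation is slight. It is tempting to argue that activity logged by centre staff has a higher ICC. That is plausible but undocumented, and Table 1 also has caregivers recording activity and a researcher testing mobility.
- Centres are to be randomised within blocks of similar centres where possible. To the extent that blocking balances differences between centres, the inflation is smaller than calculated.
- The result at the stated cluster size of 7 is 1.7 times nominal (8.6/5). It reaches 2.0 times (10.0/5) only at the 9.3 per centre implied by the total.

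**Conclusion.** The concern holds for the first-step tests. The protocol states an analysis of effectiveness at p < 0.05 that ignores the unit of randomisation and conflicts with its own sample-size reasoning. With ICC 0.05 the true two-sided size of those tests is about 8.6% to 10.0%, and their standard errors are about 12% to 16% too small. Over assumed ICCs of 0.01 to 0.10 the size is about 6% to 15%.

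These figures assume centres of equal size and no gain from blocking. They describe the first-step p-values only. The planned mixed model, the design and the data are untouched, so this is a correction to the stated analysis and not a flaw in the trial's main inference.

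**What to change.** Reword the first stage as descriptive: means and percentages by arm, without p-values. State that all inference on effectiveness comes from the mixed model with a random effect for day-care centre. If a simple test is wanted beside the model, run a t-test on the 24 centre means (24 − 2 = 22 degrees of freedom).

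This changes about one sentence of the Effect evaluation section. The only thing lost is the set of naive p-values; no additional data are needed. The Trial status section says data collection was still under way when the article was first submitted, so on that timetable the wording could be settled before the final analysis.

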### Control group: Regular activities

Participants with dementia in the day-care centres in the control group can join the regular activities. This can be a variety of recreational activities, as well as physical exercise activities such as gymnastics in a group setting, walking outdoors, etc. Day-care centres in the control group are also entitled to the same discount on the exergaming equipment and the list of optional funding organizations. However, they will not use the exergaming equipment yet for the duration of the trial.

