Physical functioning of the participant living with dementia	Physical Activity Scale of the Elderly (PASE) [67]	Researcher during interview	X	X	X	
Fall incident rate of the participant with dementia during the past 3 months	Custom-developed registration form	Informal caregiver	X	X	X	
- Behaviour and mood of the participant living with dementia - Emotional burden for the informal caregiver	Neuropsychiatric Inventory-Questionnaire (NPI-Q) [75, 76]	Researcher during interview	X	X	X	
For both informal caregiver and participant with dementia: - Demographics and personal characteristics - Physical functioning - Cognitive functioning - Social functioning - Emotional functioning - Quality of life - Healthcare costs Experiences of the informal caregiver	The Older Persons and Informal Caregivers Survey Minimum DataSet (TOPICS-MDS informal caregiver) including EuroQol five dimensions questionnaire with five-level scale (EQ-5D-5 L) [72–74]	Researcher during interview	X	X	X	
Subjective burden for the informal caregiver	Short Sense of Competence Questionnaire (SSCQ) [77]	Researcher during interview	X	X	X	
Positive care experiences of the informal caregiver	Scale of Positive Experiences (Positieve Ervaringen Schaal (PES)) [78]	Researcher during interview	X	X	X	
- Healthcare costs - Unexpected (Adverse) Events, falls and reasons of (potential) drop out	(Care) diaries (one for the participant living with dementia, one for the informal caregiver)	Informal caregiver				X
Experience of the participant living with dementia with sports/cycling, technology and digital games in the past	Separate questions	Researcher during interview	X

**Table 4 Tab4:** Secondary outcome measures for staff at day-care centres

Outcome	Outcome measure	Recorded by	Timing		
			Baseline	3 months	6 months
- Fall incident rate of the participant with dementia during the past 3 months - Social context and extent of supervision during the exergaming activity (*only* experimental group)	Custom-developed registration form	Staff at day care centre	X	X	X
Social functioning of the participant living with dementia in the day care centre	GIP: Behaviour Observation Scale for Intramural Psychogeriatrics: sub scale 1 (Gedragsobservatieschaal voor de Intramurale Psychogeriatrie (GIP): subschaal 1) [79]	Staff at day care centre	X	X	X

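### The confounder step lists equipment type, which exists only in the exergaming arm, and undefined staff support as adjustment candidates, and picks covariates by how far they move the treatment effect

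*Protocol article*

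**What the plan says.** The rule is in the protocol article, Analysis of the data, Effect evaluation. It works in steps.

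- **Entry.** A variable becomes a candidate under this condition: "If any differences in variables related to the outcome measures between the experimental group and the control group are found at baseline". No test or cut-off is given for a difference.
- **Retention.** Each candidate is added to the model for each outcome to "check whether the uncorrected Beta-coefficient (β) changes with more than 10%, which means that this variable will remain in the model as a confounder".
- **Use.** The mixed models for 3 and 6 months are then run "with the selected confounders included in the analysis".
- **Examples.** "Examples of potential confounders are type of exergaming equipment, amount of support from staff, severity of dementia etc".

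Four other places bear on the first two examples.

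- **Control group: Regular activities** says of the control centres that "they will not use the exergaming equipment yet for the duration of the trial".
- **Recruitment and randomization day-care centres** pairs a centre that already owns equipment with one that does not. If the pair is allocated to control, "the day-care centre without the equipment will participate in the trial".
- **Table 4** (staff outcome measures) lists "Social context and extent of supervision during the exergaming activity", marked as experimental group only and scheduled at baseline, 3 and 6 months.
- **Harms, Risk/benefit assessment** says that a staff member supervises the exergaming, so supervision is part of delivery.

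**The concern.** A confounder in a two-arm comparison must be defined in both arms and must not be produced by the allocation. Equipment type fails the first condition. Staff support may fail both, depending on what is meant.

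The estimate at stake is exergaming against regular activities. Study design and setting says the comparator was chosen so that any between-group effect can be put down to exergaming. If the model conditions on a feature of exergaming, its arm coefficient answers a different question or has no answer.

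A separate problem is that the 10% step judges each covariate by its influence on the estimated treatment effect. Which covariates enter, and so the reported result, then depends on the data the trial is meant to test.

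**Working it through.** **1. The plan's own figures, to set a scale.** Sample size calculation gives a difference of 2, SD 4.6, power 80%, alpha 0.05, ICC 0.05, 7 dyads per cluster and 4% drop-out.

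- Unclustered: 2 × (1.96 + 0.84)² × 4.6² / 2² = 82.9, so 83 per arm and 166 in total, as stated. The t-based calculation gives 84 per arm, 168 in total.
- Design effect: 1 + (7 − 1) × 0.05 = 1.30. Then 166 × 1.30 = 215.8, and 215.8 / 0.96 = 224.8 (stated: 224).

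These figures reproduce. The point does not depend on them. They concern the MMSE, a secondary outcome, and serve below only as a scale.

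**2. Is equipment type defined in the control arm?** Individually enrolled control centres do not use the equipment. In a pair allocated to control, the unequipped centre takes part. So every control centre has the value none, and every exergaming centre has a system.

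**3. Consequence for the model.** Four systems are offered at a discount (Intervention and materials). Take four types as the illustration.

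- Full coding: intercept + arm + 4 type indicators = 6 columns. The type indicators add up to the arm indicator, so the rank is 5 and the arm effect is not identifiable. This holds for any number of types.
- One type dropped: the arm coefficient becomes the dropped system against control.
- Controls left missing: a complete-case fit loses the whole control arm.

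For precision in the second case, assume 12 centres per arm of equal size and 3 centres per type. The variance is then proportional to 1/12 + 1/3 = 0.4167, instead of 1/12 + 1/12 = 0.1667. The ratio is 2.5, so the SD is √2.5 = 1.58 times as large. A simulation of 4,000 runs (24 centres × 9 dyads, ICC 0.05, SD 4.6, true effect 2) agrees: the empirical SD rose from 0.75 to 1.18, a ratio of 1.57. The systems were simulated as equally effective, so the mean stayed near 2 (2.02 and 2.01). If they differ, the coefficient also targets a different quantity.

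**4. Staff support, if it means supervision during exergaming.** Two cases, both under assumed values.

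- *Coded 0 in controls and unrelated to outcome* (assumed mean 2, SD 0.5 in the exergaming arm). The arm coefficient is extrapolated to zero supervision, 2 / 0.5 = 4 SDs below the mean. The mean stayed at 2.03, but the empirical SD rose from 0.75 to 2.01.
- *Measured in both arms, raised by the intervention, and carrying a share f of the effect.* The adjusted coefficient is 2 × (1 − f). Power below is Φ(δ / (4.6 × √(2/84)) − 1.96), the unclustered equivalent with an unchanged standard error.

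| f | expected coefficient δ | power |
|---|---|---|
| 0 | 2.0 | 80% |
| 10% | 1.8 | 72% |
| 25% | 1.5 | 56% |
| 50% | 1.0 | 29% |
| 100% | 0 | – |

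The simulation at f = 50% gave 1.02, against 2.02 unadjusted. The relative change in the coefficient is f, so in expectation the second step retains such a variable once f exceeds 10%.

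**5. The 10% threshold.** Adding a covariate with outcome slope γ and between-arm baseline difference d moves the coefficient by about γd. The covariate stays if |γd| > 0.10 × |β|. The left side does not depend on the treatment effect, but the threshold does: 0.2 points when the estimate is 2, and 0.1 points when it is 1. The nearer the estimate is to zero, the smaller the chance imbalance that suffices. The entry step limits which covariates reach this threshold, by an amount that the missing cut-off leaves open.

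**The case against.** The strongest defence is that the rule has two steps. A covariate must first differ between arms at baseline, and a strict reading of that step would admit few ordinary covariates and weaken the dependence on the observed effect. This stands. A reader might infer from the 10% step alone that most covariates will be kept when the effect is near zero. The article does not support a retention percentage, because any such figure depends on a cut-off it does not state. The entry step does not rescue equipment type, which differs by arm by construction and is named by the plan itself.

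Other stronger readings are also unsupported.

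- *The named variables are always kept, in every final model.* The text gives examples of potential confounders, selected per outcome. Under full coding there is no adjusted coefficient to compare, so the failure would be visible. The first step also yields an uncorrected coefficient for each outcome.
- *Staff support is certainly the exergaming-only item.* The term is not defined, and the plan compares day-care staff between groups at baseline. General staff support measured then in both arms would be a legitimate covariate. However, the only related measure listed is supervision during exergaming.
- *The data are already in, so the choice is being made after the fact.* Trial status says collection was still ongoing at initial submission.

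It is also fair that an article may leave the full covariate list to an analysis plan. The point here is what the article states: the named examples and the selection rule.

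**Conclusion.** The point holds in this form. Equipment type cannot serve as a confounder in this trial. That follows from the plan's own text and needs no numerical assumption. Entered with arm, it makes the arm effect non-identifiable or changes it to one system against control. The 1.58-fold SD assumes four types spread evenly over 12 equal centres.

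Staff support is a conditional problem. If it is the exergaming-specific supervision item, adjusting for it could remove part of the effect. The size depends on the share carried, for which the documents give no value. If it is general support at baseline in both arms, there is no objection. Severity of dementia, the third example, is a sound baseline covariate.

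The selection rule makes the covariate set depend on the observed imbalance and treatment effect. The direction is clear, but its strength cannot be quantified from the article.

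**What to change.** 1. Delete equipment type and any exergaming-specific support or supervision from the adjustment candidates. Use them only descriptively within the exergaming arm.
2. Define staff support, and allow it as a covariate only if it is a baseline variable measured in both arms.
3. Replace the baseline-difference and 10% rule with a short list of baseline covariates, for example the baseline value of the outcome, baseline MMSE, age and sex. Fix the list before outcome data are compared between arms.

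The cost is a change of analysis wording only. Baseline MMSE and demographics are already in the measurement schedule (Table 2), so these examples need no new data.
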